### Compliance

Compliance (primary outcome) measurements will commence after randomisation (i.e. after treatment and at the start of the allocated intervention), and will take place weekly for the duration of the program (8 weeks). These measurements will gather information for each athlete on the number and sets of executed exercises. In addition, online questions will be asked regarding the clarity of the instructions provided, difficulty of the exercises and recurrence of an ankle sprain.

### Cost diary

In order to evaluate the cost-effectiveness of the allocated interventions, athletes who sustain an ankle sprain recurrence will be contacted by phone to obtain information on costs associated with treatment. Based on this information direct and indirect costs resulting from the sustained ankle sprain recurrence will be calculated for use in an economic evaluation. The economic evaluation will be performed from a societal perspective.

### Cost-effectiveness evaluation

Costs of the allocated intervention will include costs that are directly related to the implementation of the allocated intervention program. These costs include the written information materials, the development and maintenance of the application, and the balance boards. In addition to the cost of the intervention itself, direct health care costs will be included, i.e. costs of care by a general practitioner, physiotherapist, massage therapist, alternative therapist, sports physician or medical specialist (e.g., orthopaedic surgeon, general surgeon); hospital care, use of drugs (e.g. acetaminophen, ibuprofen) and the use of medical devices (e.g., crutches, tape, braces). The costs of drugs will be estimated on the basis of prices recommended by the Royal Dutch Society of Pharmacy [14]. Also, indirect costs resulting from a loss of production due to absenteeism from paid or unpaid work will be included. Indirect costs for absenteeism from paid work are calculated using the friction cost approach of 4 months, based on the mean age and sex specific income of the Dutch population. Indirect costs for productivity loss of unpaid work, such as study and household work, costs are estimated at a shadow price of €8.30 an hour [15].

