### Objectives

The objective of this randomised controlled trial is to evaluate the implementation value of the ‘Strengthen your ankle’ App as compared to the usual common practice of providing injured athletes with written materials.

Our hypothesis is that the use of the ‘Strengthen your ankle’ App will increase compliance to the prescribed neuromuscular training program and, consequently, will decrease ankle sprain recurrence incidence.

Specific research questions that will be answered are:

• What is the compliance to the prescribed 8-week exercise program via the App and via written material?

• Is there a difference in program compliance rates between the ‘Strengthen your ankle’ App and written materials?

• Is there a difference in ankle sprain recurrence incidence rates during a 12-month follow-up, between groups applying the ‘Strengthen your ankle’ App and written materials?

• Is there a difference in direct and indirect costs during a 12-month follow-up, between groups applying the ‘Strengthen your ankle’ App and written materials?

• Is there a difference in ankle sprain residual complaints (i.e. instability, feeling of giving way, pain, and continued sports participation) after a 12-month follow-up, between groups applying the ‘Strengthen your ankle’ App and written materials?

• What is the participants’ user experience of the ‘Strengthen your ankle’ App and the written materials?

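### The societal cost comparison gives athletes' training time no value, which leans towards the App if the App raises compliance as hypothesised

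*Protocol article*

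**What the plan says.** All references are to the Protocol article.

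- Cost diary sets the viewpoint: "The economic evaluation will be performed from a societal perspective". It also says who supplies cost data: "athletes who sustain an ankle sprain recurrence will be contacted by phone to obtain information on costs associated with treatment".
- Cost-effectiveness evaluation gives a scope rule, "Costs of the allocated intervention will include costs that are directly related to the implementation of the allocated intervention program", and then the items: "These costs include the written information materials, the development and maintenance of the application, and the balance boards". Health care costs follow. The last category is production loss: "indirect costs resulting from a loss of production due to absenteeism from paid or unpaid work will be included". For unpaid work, "costs are estimated at a shadow price of €8.30 an hour".
- Objectives states the hypothesis that the App "will increase compliance to the prescribed neuromuscular training program" and thereby lowers recurrence. Sample size sets the contrast at 25% full compliance with the booklet against at least 50% with the App.
- Compliance describes a weekly record for every athlete over the eight weeks: "These measurements will gather information for each athlete on the number and sets of executed exercises".
- Statistical analyses promises sensitivity analyses for the cost-effectiveness ratio without naming any.

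**The concern.** A societal perspective asks what resources are used, whoever bears them. Here the main input that athletes themselves supply is their time, and no listed item covers it. It is not an intervention cost and it is not absenteeism. The phone contact would not pick it up either, since that reaches only athletes with a recurrence and asks about treatment.

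The omission would do little harm if training time were equal in the two arms, but the trial is built on the expectation that it is not. Both arms get the same balance board, so boards cancel, and neither the booklet nor the App cost is tied to how much an athlete trains. The one input that rises with compliance, and is supposed to produce the benefit, is priced at zero, while the recurrences it averts are counted in full. If the hypothesis holds, the cost difference, the cost-effectiveness plane and the acceptability curve all lean the same way. The App could be reported as cost-saving to society when part of the saving was bought with athletes' unpriced time.

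**Working it through.** **The plan's own figures.** The article states no time cost and no expected cost difference, so neither can be reproduced. The inputs used below can be checked:

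- Annual cost (Background): 530,000 × €360 = €190,800,000, as stated.
- Compliance contrast (Sample size): 25% against 50%, two-sided alpha 0.05, power 0.90 (the stated beta of 0.90 read as power). The usual two-proportion formula gives 77 per arm, 154 in total, within 3% of the stated 158.

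**Inputs from the article.** Gain in full compliance 0.50 − 0.25 = 0.25; unpaid time €8.30 per hour; mean cost of a sprain €360; programme length 8 weeks; net return of the programme €100 per package (Background).

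**Assumptions.** Session length and frequency are not in the text. For illustration only, take 5 to 30 minutes, one to three times a week. Athletes who are not full compliers are first taken to do no training.

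**Omitted cost per App athlete** = 0.25 × H × €8.30, where H = 8 × sessions per week × minutes / 60 is the hours per full complier.

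- 1 × 5 min: H = 0.67 h, cost €1.38
- 3 × 10 min: H = 4 h, cost €8.30
- 3 × 30 min: H = 12 h, cost €24.90

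If the other athletes do half the programme, these halve: €0.69, €4.15 and €12.45. Dividing the full amounts by €360 gives the absolute reduction in recurrence that would offset them: 0.4, 2.3 and 6.9 percentage points.

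**Could this change the sign of the cost difference?** Saving per App athlete = 0.25 × r × (1 − RR) × €360, where r is the 12-month recurrence risk without compliance and RR the risk ratio in compliers. Neither is given for this trial.

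- Assuming r of 20% to 50% and RR of 0.25 to 0.80, the saving runs from 0.25 × 0.20 × 0.20 × 360 = €3.60 to 0.25 × 0.50 × 0.75 × 360 = €33.75. This overlaps the range of the omitted cost.
- Example: r = 30% and RR = 0.5 give €13.50. Break-even is H = 360 × 0.30 × 0.5 / 8.30 = 6.5 h, or about 16 minutes a session at three sessions a week.
- The €100 net return points the other way. If it arose from about 25% compliers and scales with compliance (an assumption), the extra 25 points are worth about €100 per athlete. Break-even is then 100 / 0.25 / 8.30 = 48 h per additional complier, about 6 h a week, against at most 12 h in the assumed range. That scaling is itself strained: 100 / 0.25 / 360 = 1.11 sprains averted per additional complier.

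The costs of the booklet and the App also enter the difference and are not given, so its starting sign is unknown.

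**The case against.** A reader might infer that the omission reverses the economic result, or that the article contradicts itself by pricing one unpaid hour and not another. The document supports neither.

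- **Reversal.** It would need session minutes, recurrence risk, and App and booklet costs, none of which are given. The €100 net return, scaled with compliance, would put reversal out of reach of the assumed sessions. That scaling fits poorly with €360 per sprain, so it does not settle the matter, but reversal remains unproven.
- **Contradiction.** The €8.30 is stated for lost unpaid work such as study and household tasks. Balance exercises may displace leisure or other training and cost no production. Whether to value that time is a costing convention, and at a value of zero there is no bias. This stands, and it is why the rate should not be imposed on the base case.
- **Condition.** The lean exists only if the App raises compliance. With equal compliance the omitted cost cancels. This also stands.
- **Condensed text.** The word *include* need not be exhaustive, and a fuller document may say more. That is fair, but the article does itemise its categories and a unit price, and the resulting scope leaves out the athletes' main contribution.
- **Precision.** Assuming 30% recurrence at exactly €360 each, the standard deviation of cost is 360 × √(0.3 × 0.7) = €165. The 95% half-width for the difference is 1.96 × 165 × √(2/79) = €51 with 79 per arm, or €33 with 190 per arm. The omitted item lies inside either. This limits the weight of the point, but a shift in a predictable direction still moves the plane and the acceptability curve.

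**Conclusion.** The point holds in a conditional form. Under the declared societal perspective, the itemised costs give training time no value. If the App raises compliance as hypothesised and that time has any value, incremental societal cost is understated in the App's favour. The amount is about €1 to €25 per athlete for the assumed sessions at €8.30 per hour, with other athletes doing no training, and half that if they do half the programme. It rests on session lengths that the article does not give and on a valuation choice that it does not make. A change of sign is possible under some assumed inputs and not under others, so it should not be claimed. Cost-effectiveness is a secondary outcome and the primary compliance comparison is untouched. The matter is a worthwhile improvement to the economic analysis and a limit on what may be concluded from it.

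**What to change.** Leave the base case as it is. In Statistical analyses, name one of the promised sensitivity analyses as adding athletes' training time in both arms:

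- Compute each athlete's time from the exercises and sets already reported weekly, using a range of minutes per set fixed before the data are seen.
- Value it over a range of hourly prices from €0, which returns the base case, to the €8.30 already used for unpaid work.
- Carry it through the bootstrap, the cost-effectiveness plane and the acceptability curve.
- Describe the App as cost-saving from a societal perspective only if that holds across this analysis.

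No further data need be collected from athletes. The price is an assumed time per set, which the article does not supply and which is therefore given as a range, and a result for the App that may look slightly less favourable.

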### Sample size

Sample size calculations are based upon the primary outcome measure compliance, and are based upon previously established compliance rates to the same program when advocated through written materials [12]. Full compliance rates in the written materials’ group are expected to be around 25%. A doubling of this rate to at least 50% is considered to be clinically relevant. Based upon a beta of 0.90 and an alpha of 0.05 a total of 158 athletes is required divided across both study groups. In our experience from previous comparable studies the dropout rate during a 12 months follow-up is about 20%. This would mean that a sample of 190 athletes is needed per group.

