### Recruitment of study population

Physical therapy and physician practices will aid in the recruitment of athletes. Participating practices will be instructed on the aim, background and procedures of the study. Athletes treated for an ankle sprain at participating practices will be informed of the study by their caregiver. Athletes willing to participate, will then be contacted by the research team by phone after which they will enrol in the study.

Athletes will also be recruited through the Internet. Calls will be placed on the websites of associations of sports with a relatively high ankle sprain rate (volleyball, handball, basketball, korfball, soccer and athletics), websites of organisations participating in this study and on sports-related websites (e.g. http://www.meetingpoint.nl, http://www.runinfo.nl, etc.). Where possible, existing mailing lists of sport associations will be used to contact potential athletes directly. In addition electronic newsletters will be used for active recruitment of athletes.

The same recruitment strategy as described above has been employed successfully in two previous studies on the same topic [16,17]. In both studies a larger sample of injured athletes was successfully included, 476 and 352 athletes respectively.

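### The recruitment target contradicts itself: 158 athletes in total plus 20% dropout is printed as 190 per group, twice what the calculation gives

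*Protocol article*

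**What the plan says.** The Sample size section of the protocol article sets the trial size on the primary outcome: "Sample size calculations are based upon the primary outcome measure compliance". It expects full compliance of about 25% with written materials and says of the effect sought: "A doubling of this rate to at least 50% is considered to be clinically relevant". The error rates are given as "Based upon a beta of 0.90 and an alpha of 0.05", and the result is that "a total of 158 athletes is required divided across both study groups". The section then cites about 20% dropout over 12 months of follow-up and concludes: "This would mean that a sample of 190 athletes is needed per group".

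The section states neither the sidedness of the test nor the allocation ratio. The only other text that bears on the target is in Recruitment of study population, which says of two earlier studies recruited in the same way: "In both studies a larger sample of injured athletes was successfully included, 476 and 352 athletes respectively".

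**The concern.** The required number is introduced as a total over both groups and, after a dropout allowance, reappears as a number per group. A 20% allowance cannot turn 158 in total into 380 in total. The concluding sentence is the one a reader takes as the recruitment target, and it appears to be twice what the calculation supports.

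What is at stake is whether planned enrolment can be known from this document. Anyone who later compares achieved with planned numbers, or judges whether the trial stopped early, could reach opposite conclusions from the same lines.

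Two further slips should be corrected at the same time. The step from 158 to 190 looks like multiplication by 1.2 rather than division by 0.8, and a power of 0.90 is labelled beta.

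**Working it through.** **Inputs.** From Sample size: p₁ = 0.25, p₂ = 0.50 (difference d = 0.25), alpha 0.05, 0.90 read as power, dropout 0.20. Assumed because not stated: two-sided test, 1:1 allocation.

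**Step 1: reproduce 158.** The average-variance formula with p̄ = 0.375 is

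n per group = 2·p̄·(1 − p̄)·(z₀.₉₇₅ + z₀.₉₀)² / d² = 2 × 0.375 × 0.625 × (1.960 + 1.2816)² / 0.25² = 78.8, so 79 per group and **158 in total**.

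This is the printed figure. Other formulas at two-sided 0.05 and 90% power give these totals:

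| Formula | Total |
|---|---|
| Unpooled variance | 148 |
| Pooled variance | 154 |
| Arcsine | 154 |
| Average variance | 158 |
| Continuity-corrected | 170 |

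So 158 is a total. As a per-group number it would give 99.7% power, not 90%. The pooled formula also gives 79 per group for a one-sided test at 95% power; that is not the stated 0.90, and 158 is a total there too.

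**Step 2: reproduce 190.**

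- From the total: 158 × 1.2 = 189.6, so 190. Division gives 158 / 0.8 = 197.5, so 198.
- From the per-group number: 79 × 1.2 = 94.8, so 95. Division gives 79 / 0.8 = 98.75, so 99.

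The printed 190 is therefore the total after multiplying by 1.2. Neither inflation of 79 comes near 190 per group.

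**Step 3: compare the readings after 20% loss.** Power is by the pooled normal approximation, Φ[(d√n − 1.96·√(2p̄(1 − p̄))) / √(p₁(1 − p₁) + p₂(1 − p₂))], with n completers per group.

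| Randomised in total | Completers in total | Per group | Power |
|---|---|---|---|
| 190 | 152 | 76 | 89.7% |
| 198 | 158 | 79 | 90.8% |
| 380 | 304 | 152 | 99.6% |

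An exact calculation for the chi-square test gives 90.2% at 76 per group. With 380 randomised, 158 completers would remain even after a loss of 1 − 158/380 = 58%.

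**Step 4: the label.** A beta of 0.90 taken literally means 10% power, for which the pooled formula needs about 4 athletes per group. The value can only be the power, so beta is 0.10.

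**Step 5: the other passage.** The earlier samples described as larger are 476 and 352. Both exceed 190, but 352 is below 380. This fits a target of 190 in total.

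**The case against.** The best reply is that the intention can be worked out. Only a total of 190 follows from the arithmetic, so the fault is a two-word misprint. Moreover, both readings leave adequate power, about 90% or 99.6% after 20% loss, so the primary comparison is not endangered. Both statements are true. They limit the harm to an ambiguous target, but they do not remove it: a reader has to redo the calculation to find out which printed statement to disbelieve.

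Several narrower objections also carry weight:

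- The remark about larger earlier samples names no comparator. It suggests a target of 190 in total but does not prove it.
- The dropout slip is small. It costs six completers and about one point of power, and by the exact calculation 190 in total still reaches 90%.
- The 20% refers to 12 months, whereas the Compliance section measures the primary outcome weekly over 8 weeks. If loss by week 8 were, say, 10% (an assumption; the article gives no 8-week figure), 171 of 190 would remain, above 158. The 152 is thus a cautious figure for the primary outcome.
- The corrected 198 depends on keeping 158. The pooled formula's 154 would lead to 154 / 0.8 = 192.5, or 194 with equal groups.
- The beta label changes no number.

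These points settle the emphasis. The total versus per-group contradiction carries the finding, and the other two slips are corrections to make alongside it.

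**Conclusion.** The concern holds. The article prints a requirement of 158 in total and a recruitment target of 190 per group, and the second does not follow from the first. The target is overstated by a factor of two, 380 against 190, and no other passage resolves it. This must be corrected, because it is the article's only statement of planned enrolment.

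The dropout step and the beta label are also wrong, but minor: the first moves the total from 198 to 190, the second affects nothing.

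The exact match to 158 rests on a two-sided test, 1:1 allocation and the average-variance formula. The conclusion that 158 and 190 are totals does not depend on the choice of formula, since none of those tried gives a total near 2 × 158 = 316 for 90% power.

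**What to change.** Replace the closing sentences of the Sample size section with one consistent statement, for example:

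> With power 0.90 (beta 0.10), two-sided alpha 0.05 and full compliance of 25% versus 50%, 158 evaluable athletes (79 per group) are needed. Allowing for 20% dropout, 158/0.8 = 197.5, so 198 athletes in total (99 per group) will be randomised.

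The sponsor should confirm the two-sided test and equal allocation, which the present text leaves open. If the trial is to stay at 190 in total, say so and add that 20% loss leaves 152 completers with about 90% power. If 380 is really intended, state why, and give the power of about 99.6% after 20% loss.

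The cost is a few words of text and, if 198 is adopted, eight more athletes than 190.

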### Recruitment of study population

Physical therapy and physician practices will aid in the recruitment of athletes. Participating practices will be instructed on the aim, background and procedures of the study. Athletes treated for an ankle sprain at participating practices will be informed of the study by their caregiver. Athletes willing to participate, will then be contacted by the research team by phone after which they will enrol in the study.

Athletes will also be recruited through the Internet. Calls will be placed on the websites of associations of sports with a relatively high ankle sprain rate (volleyball, handball, basketball, korfball, soccer and athletics), websites of organisations participating in this study and on sports-related websites (e.g. http://www.meetingpoint.nl, http://www.runinfo.nl, etc.). Where possible, existing mailing lists of sport associations will be used to contact potential athletes directly. In addition electronic newsletters will be used for active recruitment of athletes.

The same recruitment strategy as described above has been employed successfully in two previous studies on the same topic [16,17]. In both studies a larger sample of injured athletes was successfully included, 476 and 352 athletes respectively.

One of the drawbacks of this method of inclusion is that we have no control over the treatment that is being given or has been given for the current ankle sprain. Although ruling guidelines are considered usual care, this does not necessarily mean that caregivers are actually following these guidelines by the book. Inclusion of athletes through a limited number of controlled (para) medical caregivers would decrease this problem. However, as we have learned in previous studies, inclusion through such channels is problematic and almost always results in lower inclusion rates than expected. Even so, in the proposed study we are looking for athletes treated by a variety of (para) medical caregivers. Meaning that in the proposed study a relatively large number of different caregivers would need to be found, informed on the study, and controlled as to their given treatment. Looking at the required number of athletes we believe this would prove an undoable and unrealistic undertaking. Moreover, the proposed study is on the effect of secondary preventive measures that are being applied after treatment by the (para) medical caregiver. When the caregiver would perform inclusion, this means that randomisation needs to take place at the level of the caregiver. This further complicates the study design.

### Usual care as employed in the current study

For the current study, usual care is defined as any care the athlete might seek or receive after an ankle sprain. We also define self-treatment to be usual care in the current study. Next to treatment by a (para) medical professional 60 per cent of ankle sprains - mostly minor- is self-treated by the athlete [5]. Consequently these athletes do not receive the care as described in the below mentioned ruling guidelines.

In case the athlete does receive (para) medical care, there are two ruling medical guidelines for the treatment of ankle sprains in the Netherlands, i.e. the Royal Dutch Physiotherapy Association (KNGF) guideline [18] and the Dutch Institute for Healthcare Improvement (CBO) guideline [19]. The KNGF guideline, which is the most commonly employed, aims at optimal functional recovery of the ankle, returning to full sports participation and preventing recurrent ankle injuries. Rehabilitation consists of three phases: phase 1 which aims to reduce pain and swelling, phase 2 in which load is gradually increased and functionality is re-established and phase 3 in which normal average daily living (ADL) tasks are performed. After full rehabilitation athletes are advised to use secondary preventive measures. Whereas elite athletes could have treatment duration of up to twelve weeks, six weeks are considered sufficient for amateur athletes, according to the KNGF guidelines [18].

For the purpose of the current study we do not interfere in the athletes choice of caregiver and the caregivers’ compliance to the ruling guidelines.

